**Fig 2 pone.0274193.g002:**
[figure not shown]
Study methods flow chart. 134 participants will be assessed for elegibility, allocating 67 in each arm (experimental and control groups). COT-MHABI protocol will be applied in experimental group and regular health care interventions in control group. For both groups, outcomes will be assessed over a one-year period at baseline, by the 6^th^ and 12^th^ month, when data collection is closed and analysis begins.

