### Data collection

Outcome variables will be assessed in both study groups at the beginning of the COT-MHABI protocol, 6 months after the start of the protocol, and after the end of the protocol (12 months) using the scales detailed in Table 2. The collection will be carried out by different researchers. To minimise potential discrepancies, one researcher will allways evaluate the same participant.

**Table 2 pone.0274193.t002:** Tests and variables used in the data analysis.

Test	Outcome variable definition	Scores and Domains	Reliability
*Main outcomes*			
WHOQoL-BREF	Quality of life	**Quality of life (Total score: Min 26-Max 130)** (Domains: general QoL, health status satisfaction, physical health, psychological health, social relationship and environment)	ICC = 0.87
COPM	Self-perceived occupational performance	**Performance change**: difference between measures in self-perceived occupational performance **(Total score: Min 0-Max 50)** **Satisfaction change**: difference between measures in occupational performance satisfaction **(Total score: Min 0-Max 50)**	r = 0.87–0.88
*Secondary Outcomes*			
SOD-EO	Satisfaction with daily occupation, occupational balance and activity level	**Satisfaction (Score: Min 13-Max 91)** Activity level (Score: Min 0-Max 13) Occupational Balance (Score: profile, no min or max) (Domains: productivity, leisure, home tasks and selfcare).	r = 0.84–0.92
RCv3	Satisfaction with performed roles	**Satisfaction (Score: Min 0.00-Max 1.00)** Number of performed roles (Score: Min 0-Max 10) Participation (Score: Min 0.00-Max 1.00) Desired Performance (Score: Min 0.00-Max 1.00)	r = 0.74–1.00
ACS	Perceived activity participation level	**Percentage of maintained activities after ABI (Total score: Min 0%-Max 100%)** (Domains: instrumental activities, low physical demand leisure activities, high physical demand leisure activities, social and educational activities)	r = 0.88–0.95
CIQ	Community integration and participation	**Community integration and participation (Total score: Min 0-Max 29)** (Domains: home integration, social integration and productivity)	r = 0.83–0.93
FIM	Functional Independence	**Functional Independence (Total score: Min 18-Max 126)** (Domains: motor and cognitive)	ICC = 0.85

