#### Power analysis and sample size calculations

Theoretically, with a two-tailed test, a sample of 134 participants will be needed in order to detect a significant difference in WHOQoL-BREF showing an effect size d = 0.49 (alpha = 0.05, beta = 0.20, power = 0.80), according to data collected in Chiu et al. (2016) [47]. The sample was calculated using the GPower 3.1 program.

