### Statistical analysis

Data will be analysed on an intention-to-treat basis [61] i.e. results will be analysed using the basis of all participants. For missing data, the multiple imputation method will be used.

All variables will first be checked for normality. To test the effectiveness of the intervention, continuous variables having normal distribution will be analysed by repeated measures analysis of variance, ANOVA (within-subject factors: baseline, intermediate evaluation, final evaluation), comparing the two groups (between-group factors).

Due to the proposed design and the technical feasibility of the experimental group provider site, non-simultaneous recruitment makes the potential exposure to certain external factors unequal for some subjects. These factors may include the season of the year or the phase corresponding to the COVID-19 pandemic situation. To control them, we will explore the differences in the proportion of participants for these variables between the two groups using chi-square tests. If there are differences between groups an ANCOVA will be carry out with these external factors as covariates.

Non-normally distributed variables will be analysed using the Mann-Whitney test for group comparison. Friedman analyses and the Wilcoxon signed-rank test will be used for intrasubject factors. A p value < .05 will be defined as statistically significant. Bonferroni correction will be carried out for planned comparisons.

To determine the contribution of satisfaction with activities on quality of life in people with brain injury and a diagnosis of mental illness, beyond the intervention performed, a hierarchical regression analysis will be performed with the entire sample, including the following variables in model 1: belonging to the intervention group, age and level of functionality. In model 2, in addition to the variables in model 1, the variable satisfaction with the occupation (collected by SDO-OB) will be added.

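### Season and COVID-19 phase are to be controlled only by ANCOVA, but non-normal outcomes are assigned to rank tests that cannot carry these covariates

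*Protocol article*

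**What the plan says.** All of the relevant rules are in the Statistical analysis section of the protocol article.

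- The first step is a distribution check: "All variables will first be checked for normality". No test, significance level or rule for combining visits is named.
- Normally distributed continuous variables go to a repeated measures ANOVA with three visits and two groups.
- A separate paragraph names season and pandemic phase as external factors to which the groups may be unequally exposed, because recruitment is not simultaneous. Chi-square tests compare the groups on these factors, and then: "If there are differences between groups an ANCOVA will be carry out with these external factors as covariates".
- The next paragraph gives the other branch: "Non-normally distributed variables will be analysed using the Mann-Whitney test for group comparison". Friedman and Wilcoxon signed-rank tests cover the within-subject comparisons.

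The trial is non-randomised. Under Trial design and setting, matching covers gender, age, area of residence and diagnosis, but not calendar time. The hierarchical regression contains group, age, level of functionality and satisfaction with occupation, but neither external factor.

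Table 2 lists several bounded or coarse scores: ACS ("Percentage of maintained activities after ABI", 0 to 100%), RCv3 proportions (0.00 to 1.00), RCv3 number of performed roles (0 to 10) and SOD-EO activity level (0 to 13).

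**The concern.** The plan identifies a confounder, says that it must be controlled, and names one tool. It then commits a class of outcomes to tests that cannot use that tool. The chi-square check may show that the groups differ in pandemic phase, yet the test prescribed for a non-normal outcome cannot act on the result.

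This matters most for participation, roles and activity level. Season and public restrictions can plausibly change these directly, and several of them are recorded on scales likely to look non-normal. An unadjusted difference between groups on such a score could reflect when people were followed up and not what they received.

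The normality check is also made on the variables themselves. For a linear model, the residuals are what matter. As written, the shape of the raw score decides whether an outcome can be adjusted.

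**Working it through.** **Step 1. The plan's own figure.** Inputs from Power analysis and sample size calculations: "detect a significant difference in WHOQoL-BREF showing an effect size d = 0.49"; "alpha = 0.05, beta = 0.20, power = 0.80"; "with a two-tailed test, a sample of 134 participants will be needed". Fig 2 gives "allocating 67 in each arm (experimental and control groups". For a two-sample t-test with n per arm, the noncentrality is d × √(n/2). With the noncentral t distribution, 66 per arm gives power 0.798 and 67 per arm gives 0.804. So 67 per arm, 134 in total, reproduces. The point disputes no stated number; 67 per arm is used below.

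**Step 2. The rules side by side.**

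| Outcome | Group comparison | Can it include season and COVID-19 phase? |
|---|---|---|
| Normal | Repeated measures ANOVA, or ANCOVA if the chi-square tests show a difference | Yes |
| Non-normal | Mann-Whitney (Friedman and Wilcoxon within subject) | No |

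The ANCOVA sentence can be read in two ways. If it belongs to the normal branch, non-normal outcomes have no control. If it covers all outcomes, one non-normal variable has two prescribed group comparisons and nothing says which prevails. The text needs repair on either reading.

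**Step 3. Which outcomes are likely to take the rank route.** The plan names no normality test, so this rests on an assumed rule: Shapiro-Wilk at 5%, 134 participants, three visits with correlations of about 0.5 to 0.6, and assumed distribution shapes. Simulated failure rates:

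| Score type | Any of three visits | Month 12 only |
|---|---|---|
| Truly normal | 13% to 15% | 4% |
| Skewness 0.4 | 71% | 37% |
| Percentage score, near-symmetric | 29% to 36% | 12% to 14% |
| Percentage score, more skewed | 82% to 93% | 49% to 63% |
| 0 to 13 count | 99% | not computed |
| 0 to 10 count | 100% | not computed |
| Bell-shaped 26 to 130 total (WHOQoL-BREF range) | not computed | 4% |

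For truly normal data, the any-visit rate is mostly three chances at 5%: 1 − 0.95³ = 14%. Failure is near certain only for the short counts. For percentage scores it depends on shape, and for WHOQoL-BREF nothing in the documents points to failure.

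**Step 4. What the missing adjustment could cost.** The documents give no exposure shares or effects, so both are assumed. If the factor lowers a score by g SD and exposure is p₁ in one group and p₀ in the other, the bias in the unadjusted comparison is g × (p₁ − p₀).

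- 60% v 30%, g = 0.3: 0.3 × 0.30 = 0.09 SD
- 60% v 30%, g = 0.5: 0.5 × 0.30 = 0.15 SD

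The standard error of a difference with 67 per arm is √(2/67) = 0.173 SD. Dividing gives λ = 0.52 and λ = 0.87. With no treatment effect, the two-sided rejection rate is about Φ(−1.96 + λ) + Φ(−1.96 − λ), which is 8.2% and 14.0%. The Mann-Whitney test is slightly less efficient than the t-test for normal data (factor 3/π), which lowers these to 8.0% and 13.6%. Direct simulation of the Mann-Whitney test gives 7.7% and 12.8%. A fair summary is 7% to 14% against a nominal 5%.

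At 70% v 20% the bias is 0.15 to 0.25 SD, and simulation gives 13% to 29%.

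**Step 5. Is the missing covariate the cause?** A further simulation used a skewed 0 to 1 score in tenths, 67 per arm and no treatment effect:

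| Exposure | Mann-Whitney, g = 0.3 | Mann-Whitney, g = 0.5 | Rank ANCOVA with exposure | Chi-square check flags imbalance |
|---|---|---|---|---|
| 50% v 50% | 0.037 | 0.043 | 0.039 to 0.042 | 4% to 5% |
| 60% v 40% | 0.061 | 0.083 | 0.052 to 0.053 | 63% to 64% |
| 65% v 35% | 0.083 | 0.124 | 0.052 to 0.054 | 94% to 95% |
| 75% v 25% | 0.132 | 0.281 | 0.051 to 0.053 | 100% |

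With balanced exposure the Mann-Whitney test holds its level. With imbalance it does not, and adding the covariate restores it.

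**The case against.** The strongest reply is that the ANCOVA sentence stands in its own paragraph, is triggered by the chi-square result, and is not limited to normal variables. A reader might infer that the control exists only in the ANOVA branch; the text does not expressly say so. That part of the reply stands, and the point is therefore put as a gap on one reading and an unresolved conflict on the other. It could also be said that an adjusted rank method is the kind of detail a journal article leaves to the analysis plan. That is weaker, because the article does not stay silent: it names the tests for non-normal variables, and they take no covariate.

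A reader might also infer that most of the trial's outcomes, or its main outcome, will lose the adjustment. The documents do not support that. The near-certain failures are SOD-EO activity level and RCv3 number of roles, which are not the bolded scores in Table 2. The bolded SOD-EO score is Satisfaction (13 to 91), and the bolded RCv3 score is a 0.00 to 1.00 proportion whose shape is unknown. WHOQoL-BREF and COPM are bounded and face the same switch, but nothing shows that they would fail it.

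Finally, the imbalance may be small. Controls come from the programme's own waiting list, and the protocol says only that exposure is unequal for some subjects. With 60% v 40% and a 0.3 SD effect the error is 6.1%, close to nominal. This stands: the figures show scale and predict nothing.

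**Conclusion.** The point holds in a limited form. The plan names season and COVID-19 phase as factors to control, offers ANCOVA as the only means, and prescribes tests without covariates for non-normal outcomes. Neither the matching nor the hierarchical regression fills the gap.

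The short-count sub-scores are very likely to be affected. ACS and the RCv3 proportions may be, depending on shape. A main outcome could be, but this is not shown.

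On the assumed effect of 0.3 to 0.5 SD and exposure of 60% v 30%, the bias is 0.09 to 0.15 SD and the false-positive rate roughly 7% to 14%. It would be near nominal with balanced exposure and higher with stronger imbalance. The failure rates rest on an assumed normality test and assumed shapes. The structural conflict needs none of these assumptions. It should be corrected, and the correction lies wholly in the analysis.

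**What to change.** State that the group comparison of every outcome, whatever the normality result, uses an analysis that can carry covariates and includes season and COVID-19 phase. Suitable choices are the linear model with robust or bootstrap standard errors, and a rank-based ANCOVA or ordinal model for the short counts. Assess normality on model residuals and not on raw variables. Keep the unadjusted Mann-Whitney, Friedman and Wilcoxon tests as sensitivity analyses. Replacing the whole framework with mixed and ordinal models is not needed to close this gap.

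The cost is a change of wording and some extra modelling, with no new data or participants. The adjusted analysis must be combined with the planned multiple imputation, which takes some care with bootstrap errors. An ordinal model adds a proportional-odds assumption. For skewed scores, the effect will be a little less simple to describe.

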### Ethics

The Good Clinical Practice (GCP) guidelines of the International Conference on Harmonisation (ICH) will be taken into account to carry out this study. This guarantees the protection of the rights, safety and well-being of the trial subjects in accordance with the principles of the Declaration of Helsinki, as well as the credibility of the data obtained. Likewise, the documentation provided to the people participating in the study complies with the Organic Law 3/2018, of December 5, on Personal Data Protection (LOPD) and guarantee of digital rights of the Spanish State. It also has the approval of the ethics committee of the neurorehabilitation hospital where the intervention takes place (Fundació Institut Guttmann, ID: 2019.306). In addtition, this study protocol has a trial identifier and registry name at ClinicalTrials.gov, ID: NCT04586842.

Written, informed consent will be obtained from all participants involved in the study. The ultimate authority to stop or modify the trial is the Institut Guttmann Neurorehabilitation Hospital. Also, the study is subject to reviews/audits of the process by the hospital’s own research department, which is not actively involved in the design, collection or interventions.

### Limitations

Due to the technical feasibility of the programme, where the intervention is carried out, the clinical and social complexity of this patient profile, the lack of evidence on similar programmes and interventions, and the difficulties in finding a population in the setting that falls within the range of the inclusion and exclusion criteria, the presence of these issues that may interfere with the results and lead to bias should be highlighted.

The following have been identified as the main ones: (i) the inclusion of various aetiologies of ABI as a generalised concept, when the clinics presented by the patients may differ considerably [62]; (ii) the difficulty of knowing the influence of the different treatments that the patients in the control group may receive; (iii) the variability in the different conceptions of the construct "mental health" and its implications in the design of the protocol itself as well as in the practice on the quality of professional support that this population profile receives; (iv) due to the technical particularities of the research proposal, the therapist delivering the intervention and subsequently analysing a large part of the data is the same person, which may lead to biases in the results; (v) the heterogeneity in terms of the range of time after ABI in which the intervention takes place, as both groups have a wide range. This is because, at present, this is the first time that this type of support initiative is being provided in this region; so, patients are not screened according to the time of acquisition of the brain injury but by the importance of the current condition and their personal, occupational, social, and family issues.

## Discussion

The identified needs for the dual mental health/ABI population in their reintegration into the community are significantly related to the impairment of the deficits and their specific and major impact in daily life, causing a decrease in participation in meaningful activities, role performance, socialisation, and quality of life [10]. The identified factors of this deprivation are focused not only in the mentioned deficits but also on gaps in care such as limited availability of speciality services, financial strains, poor care coordination, and lack of tailored information, among others [3]. Regarding personal factors, an occupational identity loss appears concomitant with a devaluation of self [6].

To address these needs, the use of models and assessments such as those proposed in this study is supported by evidence. Several studies recommend the use of MOHO in mental health interventions, because of the improvement in volition, habituation, and skills [39–41], and in ABI interventions [10], due to the significant improvement in ADL performance, quality of life, and self-perceived health. Futhermore, the use of COPM and, in general, client-centred intervention oriented to occupational goal planning is recommended in community rehabilitation of ABI, even when volition is low or awareness of deficits interferes with daily performance [63], enabling the individual to feel more satisfied with his or her performance [64]. In addition, the fact that the setting of the COT-MHABI protocol is the home environment can induce a more client-centred approach, favouring the personalisation of the intervention by being in the everyday environment of the person [9].

Although there is evidence of the benefits of this kind of community-based interventions in ABI [65–68], there are few studies that develop the implications when both circumstances coexist [68,69]. This circumstance is crucial for providing adequate care. Also, focusing on occupational therapy intervention, one of the unmet needs for practitioners is the possibility of addressing the specificity of both conditions, that is, both those related to mental health and those involving deficits associated with ABI [69].

For this reason, it is necessary to propose research to assess the usefulness and effectiveness of community occupational therapy interventions like the COT-MHABI protocol that considers ABI and associated mental health issues. The aim is to add a further step in creating evidence for the problems of this ever-growing profile of patients [70,71] that go unnoticed, especially at their return to the community [2,3].

If the COT-MHABI protocol were to show significant results and show evidence in terms of improvement of the main and secondary variables, it would be a step forward in confirming that a community-based occupational therapy intervention, conceptualised from the facilitation of the development of occupational participation, increases the experience of meaning, wellbeing, and quality of life [6,10,11,23,26,27,64]. Given that the fundamental of intervention from occupational therapy is the recovery of meaningful activity performance, it implies a rethinking of the neurological patient’s role, providing support in community reintegration as an individual, as family member, and as a citizen.

Being aware of the limitations, we propose this COT-MHABI study protocol as a basis for developing more targeted community-based occupational therapy intervention programmes in this type of patient’s profile, as this is a growing population with better chances of survival and, as we have seen in the theoretical foundations outlined above, the continuity of social and health care is called into question, making them people at risk of exclusion.

We are confident that this type of intervention would have a direct impact on the individual, the family, and the referring health and social services. Considering variables, such as occupational balance or satisfaction with occupational performance, provides autonomous explorations and self-perception of competence to the person and, consequently, to their family environment and carers. Finally, the dissemination of studies such as this one could provide more information for better management of the dual situations of mental health and acquired brain injury.
